### Clinical data

At the baseline visit, we will record the clinical phenotype of CL including the number, size, morphology
^
25
^ and location of lesions. Lesion dimensions (defined as the largest diameter of the lesion) will be measured using a disposable tape measure. Individuals with more than one lesion will be asked to indicate the lesion causing greatest concern and this will be designated the “index” lesion. Individuals may indicate two or more lesions of equal concern. In those with mucosal involvement, mucosal signs and symptoms are recorded. Clinicians will then provide a subjective global assessment of CL severity using a 3-point Likert scale (mild, moderate, severe). Slit-skin smears will be collected at baseline for microscopy and species identification using polymerase chain reaction (PCR).

At each follow-up visit, we will assess lesions for the degree of re-epithelization or flattening. For those with DCL, the number of resolved lesions and percent of lesions flattened per region is recorded. Clinicians will provide a global assessment of the improvement or worsening of CL using a 5-point Likert scale (worse, no change, minor improvement, major improvement, cure). At each visit, we will record the treatment being administered and any changes since the last visit. The adverse reactions to CL treatments will be assessed including the nature and severity of the reaction, the action taken, the presumed cause and the outcome. The Common Terminology Criteria for Adverse Events (CTCAE) version 5.0 will be used for describing adverse reactions and grading their severity. Slit-skin smear samples will be collected at day 90 for test of cure if the skin lesion is not healed.

### PROMs

At baseline, Amharic or Oromiffa translations of several PROMs will be collected (
Table 1): two general measures of HRQoL, the EQ-5D-5L and the SF-36, and two skin-specific measures of HRQoL, the Dermatology Life Quality Index (DLQI) and the Children’s Dermatology Life Quality Index (CDLQI). Participants will complete the Cutaneous Leishmaniasis Impact Questionnaire (CLIQ), a CL-specific measure of HRQoL.

At the follow-up visits indicated in
Table 1, we will collect PROMs again and ask participants for their global assessment of the improvement of their CL lesion(s) using a 5-point Likert scale (better, somewhat better, same, somewhat worse, worse). The Amharic or Oromiffa translations of the Patient and Observer Scar Assessment Scale (POSAS) v2
^
26
^ will be completed by both the clinician and participant at the day 42 assessment and each subsequent visit.

### Costs

At baseline data will be collected on costs incurred by the individuals and their household that can be attributed to a member having CL and/or seeking treatment for CL including costs incurred since onset of CL symptoms. We will also collect data on household income, expenditure, and asset possession to establish a month of income and expenditure data.

At each follow up visit, cost related to CL since the last visit/admission will be collected. These will include costs of medicines, hospitalisation, consultation, transportation, and opportunity costs related to having and treating CL (i.e., missed work or school). We will also collect information on how households cope with the economic burden of CL.

Data from the provider perspective will be collected. This will include costs of training health workers, providing services, medicines donated, and other service-related costs. These costs will be collected from the project’s activity and financial records; the value of any donated items will be estimated based on market prices. Where necessary, government and donor sources will be consulted for relevant cost data.

### Lived experience

Participants will be recruited to participate in an in-depth interview to capture their lived experience as individuals with CL. Data will be collected from different age groups, gender, CL phenotype and places to ensure all variations to the level of saturation, where there is no new data with additional interviews. To reach saturation, an estimated 30 adults and 10 children interviews are planned. Interviews will be conducted by members of the research team using a topic-guide covering key themes that includes how it feels living with CL, impact of the illness on the person, the care-seeking pathways followed and their experience of traditional and modern health care service use. Participant observation will be used to enrich the data on patients' treatment experiences in the health facilities.

### Immunology samples

To interrogate the dynamics of immune responses in different clinical phenotypes of CL, blood and skin lesion samples will be collected at three time points. Whole blood and dried blood spot (DBS) samples will be collected by trained phlebotomists using the PAXgene® Blood DNA and RNA tubes and 3MM DBS filter papers. Physicians will take a skin biopsy samples from each CL cohort patient on the border site of the lesion using 3MM diameter disposable punches. HLA typing will be performed to determine if there is an association of HLA type with the clinical phenotypes of CL seen in our cohort. Participants will have a skin biopsy (stored in RNA
*later*™) and blood samples taken to evaluate (i) the expression of innate and adaptive, and pro-and anti-inflammatory biomarkers using Luminex multiplex assay, (ii) changing mRNA expression level of Toll-like receptors (TLRs) and pro- and anti-inflammatory cytokines during infection, treatment and after completion of treatment using quantitative PCR (Real-time PCR).

### Data analysis

**
*
Objective 1: To assess clinical outcomes in LCL, MCL and DCL in a prospective cohort.*
**

The primary outcome is the proportion of individuals with a healed index lesion by study day 90. In line with the consensus document on clinical trial outcomes cure will be defined as 100% re-epithelialization or flattening of the index lesion. Pre-specified additional outcomes are the proportion healed at day 42 and 180. Secondary outcomes include the frequency of adverse events and measures of HRQoL life.

There are no pre-existing high-quality data on cure rates for CL caused by
*L. aethiopica*. We calculated the sample size required to measure a range of cure-rates at 90 days with varying degrees of precision (
Table 2). Based on this we aimed to recruit up to 250 participants with each CL phenotype (LCL, MCL, and DCL) across the two sites. We anticipate that mucosal leishmaniasis will be rare and will recruit as many individuals with this type of disease as possible.

**Table 2. T2:** Sample sizes required to detect a range of cure rates with varying precision at day 90.

**Sample size**		**Percentage cured at 90 days**			
		50	60	70	80
	50	±13.1	±13.6	±12.7	±11.1
	100	±9.8	±9.6	±9.0	±7.8
	150	±8.0	±7.8	±7.3	±6.4
	200	±6.9	±6.8	±6.4	±5.5
	250	±6.2	±6.1	±5.7	±5.0

**
*
Objective 2: To assess clinical parameters in LCL, MCL and DCL in a prospective cohort.*
**

We will use descriptive statistics (means, medians, and proportions) to describe demographics and baseline characteristics of the cohort. In exploratory analysis, we will use univariable logistic regression to examine clinical and demographic variables associated with resolution of CL at Day 42, 90, and 180. Whilst not formally powered for these analyses, the findings will be viewed as hypothesis-generating and potentially form the basis for future studies.

**
*
Objective 3: To assess the change in HRQoL associated with CL before and after treatment.*
**

Changes in general, skin and CL-specific HRQoL will be assessed using the following PROMs: EQ-5D-5L, SF-36, DLQI/ CDLQI and CLIQ applied at the timepoints shown in
Table 1, and compared with clinical outcomes to determine validity and responsiveness.

**
*
Objective 4: To develop a severity scale for CL.*
**

A round table CL expert discussion forum, informed by preliminary data, will be held, and consensus reached about potential items and scoring system for a severity scale. The prototype will be tested in individuals with CL at diagnosis.

**
*
Objective 5: To understand the lived experiences of individuals with CL.*
**

Recordings will be transcribed and translated verbatim, and interviewer’s notes included for each interview. A codebook will be developed, and thematic analysis will be used.

**
*
Objective 6: To assess household costs of CL, and health care provider, and societal costs of treating CL.*
**

We will assess costs from a disaggregated societal perspective, examining costs to providers (MOH, donors), households, and society as a whole (i.e., costs to providers and household combined). Incremental costs to providers will be estimated relative to a hypothetical counterfactual in which no treatment for CL is provided. Incremental costs to households will be estimated relative to a hypothetical counterfactual in which the CL infection has not occurred. We will estimate total costs of diagnostic and treatment strategies and average costs, including cost per case diagnosed and cost per case resolved, disaggregated by site, type of CL, and patient characteristics (where possible), with appropriate statistical measures of variation. We will explore the degree of impoverishing and catastrophic expenditure for families of individuals with CL.

**
*
Objective 7: To characterise how cell-mediated immune responses associate with treatment responses in CL due to L. aethiopica and (HLA) variation correlate with different clinical phenotypes.*
**

Biopsies of affected skin and blood samples will be analysed to (i) evaluate secretion and quantification of selected host cytokines via the LuminexⓇ platform, (ii) evaluate the expression of innate/adaptive, and pro-and anti-inflammatory biomarkers and by evaluating the change in mRNA expression level of TLRs and pro- and anti-inflammatory cytokines before treatment, during treatment, and after completion of treatment.

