### Timelines

Study recruitment began in April 2022 and is expected to continue until the sample size is reached or until the cut-off of September 30th, 2023, whichever occurs first. Follow-up is therefore expected to be completed by September 30th, 2024.

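### Table 2 prints ±13.1 for 50 participants at a 50% cure rate; the rest of the table implies ±13.9, so one planning half-width is about 0.8 points too small

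*Protocol article*

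**What the plan says.** Under Data analysis, Objective 1, the endpoint is a single proportion: "The primary outcome is the proportion of individuals with a healed index lesion by study day 90". The article then explains the basis of the sample size: "We calculated the sample size required to measure a range of cure-rates at 90 days with varying degrees of precision". Table 2 holds the result, with sample sizes of 50, 100, 150, 200 and 250 down the side and cure rates of 50, 60, 70 and 80% across, under the heading "Percentage cured at 90 days". The row for 50 participants reads "13.1 ±13.6 ±12.7 ±11.1".

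The recruitment target follows from the table: "Based on this we aimed to recruit up to 250 participants with each CL phenotype (LCL, MCL, and DCL) across the two sites". Under Timelines, recruitment runs "until the sample size is reached or until the cut-off of September 30th, 2023, whichever occurs first". Mucosal leishmaniasis has no numerical target: "We anticipate that mucosal leishmaniasis will be rare and will recruit as many individuals with this type of disease as possible".

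**The concern.** Reading along the row for 50 participants, the half-width rises from 13.1 at a 50% cure rate to 13.6 at 60%, then falls. A proportion does not behave like that. Its variance is proportional to p(1 − p), which peaks at 50%, so the first column should be the widest in each row. It is in the other four rows.

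Table 2 is the only sample-size justification that the article shows for the primary outcome. The targets are upper limits and there is a calendar cut-off, so the smaller rows have a purpose: they tell the reader what precision remains if a phenotype falls short. A wrong entry there misstates the expected precision, and in this case makes it look better than it is.

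**Working it through.** **Inputs.** All come from Table 2: the sample sizes, the cure rates and the 20 printed half-widths. The article gives no confidence level or interval method. I took the two-sided 95% normal approximation as the candidate and tested it against every cell.

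**Formula.** Half-width in percentage points = 100 × 1.96 × √(p(1 − p)/n).

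**Step 1: reproduce the table.** Each entry shows computed / printed.

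| n | 50% | 60% | 70% | 80% |
|---|---|---|---|---|
| 50 | **13.86 / 13.1** | 13.58 / 13.6 | 12.70 / 12.7 | 11.09 / 11.1 |
| 100 | 9.80 / 9.8 | 9.60 / 9.6 | 8.98 / 9.0 | 7.84 / 7.8 |
| 150 | 8.00 / 8.0 | 7.84 / 7.8 | 7.33 / 7.3 | 6.40 / 6.4 |
| 200 | 6.93 / 6.9 | 6.79 / 6.8 | 6.351 / 6.4 | 5.54 / 5.5 |
| 250 | 6.20 / 6.2 | 6.07 / 6.1 | 5.68 / 5.7 | 4.96 / 5.0 |

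Nineteen cells agree to one decimal, including the other three in the row for 50. The exception is n = 50 at 50%: 100 × 1.96 × √(0.25/50) = 13.86, against 13.1 printed. The gap is 13.86 − 13.1 = 0.76 points, or 13.9 − 13.1 = 0.8 as printed.

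**Step 2: check without assuming a confidence level.** Under the normal approximation, whatever its multiplier, half-widths scale with √(p(1 − p)) and 1/√n. Neighbouring printed cells therefore predict the doubtful one:

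- From n = 100 at 50%: 9.8 × √(100/50) = 13.86. Allowing for rounding of 9.8 (9.75 to 9.85), the range is 13.79 to 13.93.
- From n = 200 at 50%: 6.9 × √(200/50) = 13.8, with a rounding range of 13.7 to 13.9.
- From n = 50 at 60%: 13.6 × √(0.25/0.24) = 13.88.

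None of these is compatible with 13.1.

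**Step 3: check other interval methods for n = 50 at 50%.**

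| Method | Half-width |
|---|---|
| Multiplier 2 instead of 1.96 | 14.14 |
| Wilson | 13.36 |
| Agresti-Coull | 13.36 |
| Jeffreys | 13.53 |
| Clopper-Pearson | 14.47 |
| Denominator n − 1 | 14.00 |
| Continuity correction | 14.86 |
| 90% level | 11.63 |

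None gives 13.1. The Wilson, Agresti-Coull, Jeffreys and Clopper-Pearson intervals are also wider at 50% than at 60% for n = 50 (Wilson: 13.36 against 13.11). The reversed order is therefore not explained by the choice of method.

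**Step 4: what ±13.1 would mean, if the table is at the 95% level.** A half-width of 13.1 at 50% needs n = 0.25 × (1.96/0.131)² = 55.96, about 56 participants rather than 50. With 50 participants, the multiplier implied by 13.1 is 0.131/√(0.25/50) = 1.853, which corresponds to about 93.6% coverage.

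**The case against.** The arithmetic is hard to dispute. The case on the other side is that little depends on it, and most of that case stands.

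- **The target does not rest on this cell.** It rests on the row for 250 participants, where all four entries are right. A reader might infer that the sample-size justification is unsound. It is not: no stratum is planned at 50, and no analysis or stopping rule uses ±13.1.
- **No small stratum is forecast.** A reader might infer that a rarer phenotype will close near 50 and be reported with falsely high precision. The article gives no expected split by phenotype and does not predict that LCL, MCL or DCL will end near 50. Study context puts the two centres at roughly 1000 and 700 diagnoses a year. The only form expected to be rare is mucosal leishmaniasis, and the article sets no target number and claims no precision for it.
- **Planning figures are not results.** Any reported interval will come from the observed number and proportion, so none will be too narrow because of this entry.
- **The least favourable figure in the row is nearly right.** A reader who takes the largest entry sees ±13.6, which is only about 0.3 points short of 13.9. The 0.8-point gap affects someone who reads the 50% column.
- **The 95% level and the method are inferred.** The 56 participants and the 93.6% depend on that inference. The reversed order within the row does not.

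A fault in the text extraction cannot be excluded altogether. However, the row has four aligned values and the other three are correct, so nothing points to one.

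What does not stand is leaving the cell alone. It is a wrong figure, stated in the table that justifies the sample size.

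**Conclusion.** The entry for 50 participants at a 50% cure rate is wrong as printed, most probably through a typing error. It should be ±13.9, so the planning half-width is understated by about 0.8 percentage points in one cell of 20. That it is wrong follows from the table's own pattern. That the right value is 13.9 rests on the inferred 95% normal approximation, which the other 19 cells support. The consequence is minor: the row for 250, the target of up to 250 per phenotype, recruitment and the analysis are all unaffected.

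**What to change.** In Table 2, replace ±13.1 with ±13.9 in the cell for 50 participants at 50% cured. This costs one table entry and a slightly less favourable planning figure. If the authors confirm the confidence level and method, a short note under the table would let readers check it, but the correction does not depend on that. No reporting rule for small phenotypes should be added.

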*L. aethiopica*. One study reported physician-determined cure rates of 59.7% for intralesional SSG
^
18
^ at Day 90, whilst another study reported physician-determined cure rates of 12.5% and 72.7% for miltefosine
^
19
^ at two study sites at Day 90.

The “harmonized” clinical research methodologies for LCL provided a significant step forward but several gaps remain. No agreed methodologies are available for assessing flattening or re-epithelisation and it remains unclear if outcomes should be measured from the start or end of a course of treatment. The agreed outcome measures are entirely clinical and do not include measures to reflect the outcomes and experiences of affected individuals. The treatment preferences of individuals may be influenced by the frequency of adverse events and the extent to which healing improves their health and psychosocial wellbeing. Appropriate patient reported outcome measures (PROMs) therefore need to be identified and collected alongside clinical measures. Finally, the consensus document recognised that scarring should be assessed as a long-term outcome but did not propose a method for doing so.

Given the scarcity of resources for health, and for the treatment of CL in particular, treatment recommendations should also be informed by an understanding of costs and efficiency. However, cost-effectiveness analyses of alternative treatment strategies for non-American CL have only been conducted in Asia
^
20–
23
^, none have addressed infection with
*L. aethiopica*, and only one has assessed effectiveness using a multidimensional outcome metric
^
20
^, which is essential for comparing the value of investments across intervention types and diseases. No studies of the economic burden of CL or treatment costs in Africa have been published. 

The Ethiopian Federal Ministry of Health (FMOH) has identified an urgent need for the evaluation of treatments alternatives for all forms of CL. Such evaluation requires better understanding of outcomes, and cost-effectiveness data. We therefore designed an observational, multi-centre cohort study of CL in Ethiopia
^
24
^.

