### Study participants and management

Adults and children with CL who are managed as inpatients or outpatients are eligible to participate in the study.

Inclusion Criteria: Participants with laboratory confirmed CL

Exclusion Criteria: Participants who have previously been treated with systemic anti-leishmanial therapy

Participants will be treated using the standard of care for CL at the centre where they are managed and in accordance with the Ethiopian national guideline
^
24
^ which will be agreed by two clinicians in consultation with the affected individual prior to enrolment. The treatment may be changed if deemed clinically appropriate. In general, if the size of the skin lesion is 4cm in diameter of smaller and not near a mucosal site the first line treatment is most frequently local therapy (cryotherapy and/or intralesional SSG). In general, if the diameter of the skin lesion is greater than 4 cm and/or near or involving a mucosal surface the initial therapy is usually intramuscular SSG for 28 days with or without adjunctive cryotherapy. Participants will be assessed on day 42 and further local or systemic therapy may be offered depending on the degree of clinical response.

We will classify CL using the operational definitions shown in
Box 1.

Box 1. Operational definitions of Cutaneous Leishmaniasis (CL)•    CL is diagnosed in a person with skin and/or mucosal lesions with evidence of
*Leishmania* infection in the affected tissues characterised by the presence of
*Leishmania* amastigotes on smear microscopy or growth of
*Leishmania* promastigotes in culture or the detection of

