## Discussion

CL represents a major public health, psychosocial and economic problem both in Ethiopia and in the tropical – subtropical regions. A key target of the 2021-2030 WHO Neglected Tropical Diseases roadmap is a significant increase in the proportion of individuals with CL who are diagnosed and receive appropriate treatment. The 2021-25 Ethiopian strategic plan for Neglected Tropical Diseases, aims to meet the 2030 global target by increasing CL treatment centres from 14 to 30, diagnostic centres from 25 to 170 and to be able to detect 85% of cases and treat 95% of these. A better understanding of strategies to improve accessibility and treatment outcomes is a priority action to achieve this goal
^
28
^.

There are currently few prospective data of well-defined treatment outcomes for individuals with CL caused by
*L. aethiopica*, and no data on PROMs or costs. A large cohort of participants with CL will generate robust data on how outcomes are associated with key clinical characteristics such as lesion size, site and number. This will allow us to gain insights into expected clinical outcomes up to one year following treatment and accurately quantify the burden of adverse reactions associated with current treatments. There are new agents and combination therapies proposed for the treatment of leishmaniasis and our data will be valuable in helping design future trials of these approaches in individuals with
*L. aethiopica*.

This prospective cohort study will generate the most comprehensive and holistic dataset of CL, combining clinician determined and patient reported outcomes alongside health economic and laboratory data to better capture the impact of CL for affected individuals, their families, and communities. These data will inform the design of randomised trials to evaluate new treatment strategies, help improve evidence-based guidelines and support evidence-led policy decisions.

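### Objective 2 plans only univariable logistic regression for healing, although size, site, number, phenotype, centre and treatment are linked by design; this cannot support the robust associations the Discussion promises

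*Protocol article*

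**What the plan says.** Under Data analysis, Objective 2, the article states: "we will use univariable logistic regression to examine clinical and demographic variables associated with resolution of CL at Day 42, 90, and 180". It then qualifies this: "Whilst not formally powered for these analyses, the findings will be viewed as hypothesis-generating and potentially form the basis for future studies". No multivariable model and no stratification by phenotype, centre or treatment is named for this analysis.

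Other sections tie the candidate predictors together:

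- **Treatment and size or site.** Under Study participants and management, local therapy is the most frequent first choice "if the size of the skin lesion is 4cm in diameter of smaller and not near a mucosal site", and intramuscular SSG is usual "if the diameter of the skin lesion is greater than 4 cm and/or near or involving a mucosal surface". Further therapy may be offered after Day 42 according to response.
- **Treatment and centre.** "Participants will be treated using the standard of care for CL at the centre where they are managed".
- **Phenotype, number and mucosa.** Box 1 defines localised and mucocutaneous disease by ten or fewer lesions, without and with mucosal involvement respectively. Diffuse disease is eleven or more lesions, with or without mucosal involvement.
- **Recruitment.** Objective 1 aims for up to 250 participants of each phenotype across two sites.

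The Discussion says that a large cohort "will generate robust data on how outcomes are associated with key clinical characteristics such as lesion size, site and number".

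**The concern.** A model with one variable at a time attributes to that variable everything that travels with it. In a pooled analysis the OR for lesion number would largely be a contrast of diffuse with other disease, because eleven or more lesions is the definition of diffuse disease. Mucosal site overlaps with phenotype in the same way. Phenotype mix partly reflects recruitment targets and may differ between the two centres, so a crude centre OR can reflect case mix. If treatment is examined as a predictor, size and site confound it directly.

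The study is meant to inform the design of randomised trials. A trial designer choosing stratification factors needs to know whether size or location matters within a phenotype and, usually, within a treatment class. A crude OR does not answer that and may understate or hide it.

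**Working it through.** **1. The plan's own figures.** No figure is given for the regression. Table 2 gives the precision of a cure proportion. Assuming a 95% two-sided interval, the half-width at n = 250 and 50% cured is 1.96 × √(0.5 × 0.5 / 250) = 6.2 percentage points, as printed. Nothing in Table 2 addresses the associations.

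**2. Lesion size and treatment (illustration).** The documents do not give the share of patients treated according to the size guide, nor a treatment OR that holds size fixed. Assumptions:

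- 60% healed among small lesions on local therapy;
- OR for large versus small lesions within treatment, 0.50;
- concordance c, the share of large lesions given systemic and of small lesions given local therapy, 60% to 90%;
- systemic versus local OR: 1.33, 2.0 or 3.34.

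The outer treatment ORs come from crude contrasts in the Introduction. Improvement of 85% with intramuscular SSG and 81% with cryotherapy gives (0.85/0.15)/(0.81/0.19) = 1.33. Positive outcomes of 47% with systemic and 21% with intralesional meglumine antimoniate give (0.47/0.53)/(0.21/0.79) = 3.34. The value 2.0 is a chosen mid-point.

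Formula: P(healed | size) = Σ over treatment of P(treatment | size) × expit[logit(0.6) + ln(0.5) × large + ln(OR_trt) × systemic].

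Example with OR_trt = 2.0 and c = 90%. The cell probabilities are small/local 0.600, small/systemic 0.750, large/local 0.4286 and large/systemic 0.600.

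- Large: 0.9 × 0.600 + 0.1 × 0.4286 = 0.5829
- Small: 0.9 × 0.600 + 0.1 × 0.750 = 0.6150
- Crude OR = (0.5829/0.4171)/(0.6150/0.3850) = 0.87

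| Treatment OR | c = 60% | 70% | 80% | 90% |
|---|---|---|---|---|
| 1.33 | 0.53 | 0.56 | 0.59 | 0.63 |
| 2.0 | 0.58 | 0.67 | 0.77 | 0.87 |
| 3.34 | 0.66 | 0.83 | 1.05 | 1.32 |

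Every entry lies above 0.50. Only the two at the lower right exceed 1. Replacing the 60% baseline by 50% changes no entry by more than 0.01.

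**3. Centre and phenotype (illustration).** Assume 250 per phenotype, cure of 80/60/50% in the three phenotypes, no centre effect within phenotype, and one centre supplying 70/50/30% of them.

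- That centre: (0.8 × 0.7 + 0.6 × 0.5 + 0.5 × 0.3)/1.5 = 0.673
- The other: (0.8 × 0.3 + 0.6 × 0.5 + 0.5 × 0.7)/1.5 = 0.593
- Crude centre OR = (0.673/0.327)/(0.593/0.407) = 1.41

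Milder shares (60/50/40%) or milder cure rates (70/60/50%) give 1.12 to 1.25.

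**4. Feasibility of adjustment.** If all 750 are recruited and evaluable, and cure lies in Table 2's range of 50% to 80%, the rarer outcome has between 750 × 0.50 = 375 and 750 × 0.20 = 150 cases. At an assumed 10 cases per parameter that allows about 37 down to 15 parameters. Centre (1), three phenotypes (2), size (1), seven body regions (6), age (1), sex (1) and initial treatment class (1) need 13. In one phenotype of 250 the rarer outcome has 125 down to 50 cases, or about 12 down to 5 parameters.

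**The case against.** The strongest defence is that the analysis is declared exploratory, unpowered and hypothesis-generating, and is not the primary objective. Objective 2 is worded for the three phenotypes, so fitting within phenotype remains open. Treatment is not named as a predictor, and covariate lists normally belong in an analysis plan. Much of this stands and keeps the point modest. It does not remove it: the article is not silent but names a method, and its label concerns power and status, not bias. The Discussion then makes a stronger claim for the same associations.

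Three stronger readings are tempting and are not supported.

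- **That treatment confounds the size association.** Initial treatment follows from size, so it lies downstream. The crude size OR is partly a legitimate total association under current practice, which suits a study of expected outcomes. Phenotype, mucosal site and centre are the confounders there.
- **That the size effect will be reversed.** The 1.32 needs 90% concordance together with an OR of 3.34, which is a crude contrast for a drug other than the SSG used here. The article describes treatment choice only in general terms. The contrast closest to this cohort's modalities, OR 1.33, gives 0.63 even at 90% concordance, which is attenuation.
- **That a very large centre effect is to be expected.** The Introduction's "physician-determined cure rates of 12.5% and 72.7% for miltefosine" implies an OR of about 19 between two sites. It concerns a drug not listed as standard treatment here, and the article does not say that those sites are this study's centres.

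**Conclusion.** The point holds in a limited form. Univariable regression is the only method stated, the predictors are linked by design, and the resulting ORs cannot be read as robust evidence on size, site and number. The mixing with phenotype and centre, and of any treatment comparison with size and site, follows from the definitions and treatment practice in the article. Its size cannot be computed from the documents. The illustrations (0.53 to 1.32 for a within-treatment size OR of 0.50; 1.12 to 1.41 for a centre with no effect within phenotype) rest wholly on the stated assumptions. The primary outcome, a cure proportion, is unaffected. This should be changed, but it does not threaten the study.

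**What to change.** Keep the univariable table as description. Add a pre-specified multivariable logistic model at Day 90, repeated at Days 42 and 180, with centre, phenotype, index-lesion size, location or mucosal site, age and sex. Three details matter:

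- Show the model with and without initial treatment class. Without it, the size coefficient keeps the effect of treatment choice; with it, the coefficient moves towards a within-treatment association. Neither is a clean direct effect at Days 90 and 180, because treatment may change after Day 42 in response to outcome.
- Examine lesion number within phenotype, because the two overlap by definition. Mucosal involvement is likewise fixed in localised and mucocutaneous disease, so code location so that it adds information beyond phenotype.
- Limit the number of parameters by the cases of the rarer outcome actually observed. The 750 is a ceiling and recruitment has a cut-off date.

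In the Discussion, replace the claim of robust data with hypothesis-generating associations, in line with Objective 2.

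The cost is analysis-plan wording, some programming and slightly wider intervals. Size, number, location, treatment and demographics are already recorded, and phenotype and centre are known.
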